#### Patients

Patients 18 years or older visiting participating GPs during a study cycle will be asked for to provide informed consent to participate in the study. Patients suffering from moderate or severe cognitive impairment, or those of too low literacy, will be excluded. Moreover, patients who will not talk to their GP in person will be excluded (e.g., patients who just come to pick up a prescription or to escort a relative).

The study team involved in the data collection consists of four part-time researchers (Bachelor/Masters’ degree in psychology, public health, and health economics). Each researcher can manage data collection in two of the eight GP practices in each study cycle. Prior to data collection, the researchers will inform nurses in participating GP practices about the study schedule, and ask for assistance regarding patients who do not meet the inclusion criteria. Posters and leaflets promoting the study will be provided to the practices.

During a data collection day in the practice, patients will be informed about, and invited to participate in the study by the researcher in the waiting room, prior to their consultation with the GP. Consenting patients will be asked to participate in a brief interview immediately following this consultation. At this time, patients will not be fully informed about the real purpose of the study, because addressing the topic of smoking at this time could trigger patients to initiate a discussion about their smoking during the consultation. Hence, prior to the consultation, patients will be asked to participate in a study on “physician-patient communication on health behaviour”. This strategy has been approved by the ethics committee.

Brief interviews (~ 10–15 min) to collect baseline data (see Additional file 1, translated versions are also provided) will be conducted consecutively with every single patient. All patients will be asked on sociodemographic characteristics (e.g., age, sex, level of education), health-related quality of life, and on smoking status. Never and ex-smokers will receive full information on the purpose of the study and the interview will be interrupted at this moment. Patients who only use electronic cigarettes or heat-not-burn products but who do not smoke tobacco cigarettes will also be excluded at this moment. Furthermore, those patients will not be included in any follow-up data collection.

Current daily and non-daily tobacco smokers (cigarettes, cigarillos hand-rolled cigarettes, pipe, cigar, or hookah) will be further interviewed on their smoking behaviour, motivation to stop smoking [28], strength of urges to smoke [39], as well as on primary and secondary outcomes. At the end of this interview, patients will be informed about the purpose of the misinformation regarding the interview content according to the requirements of the ethics committee.

By assessing the above-mentioned primary and secondary outcomes immediately after GP consultation through a face-to-face interview, we aim to maximise response rates and minimise recall bias.

### Blinding

Due to the pragmatic nature of the study design it will not be possible to fully blind GPs to their training allocation (5A or ABC method). However, to minimise possible systematic bias, where GPs tend to make more effort in delivering brief advices to quit depending on the training method they were allocated to, we aim to reduce the information on the group allocation until the end of the 4-week pre-training data collection period. In particular, during the recruitment process and during the pre-training period, GPs will only be informed that the implementation of the brief advice in GP practices is being examined and that the effect of two different brief advice methods is compared. The GPs, however, received no information about the content and the difference of both methods.

Initially, we planned to blind the researchers conducting the baseline data collection to the GPs’ group allocation. However, with eight GPs per study cycle and four part-time researchers collecting data in their practices, it will not be feasible to conceal group allocation to the study team. In order to prevent that GPs behave differently depending on the person collecting data in their practice, these researchers will not be actively involved in the training of the GPs.

### Intervention

Depending on their group allocation, GPs will receive training on the delivery of brief stop-smoking advice either according to the 5A or to the ABC method. Both types of training will be conducted in accordance with the national and international guidelines on smoking cessation [10, 11]. In both groups, the training will be organised at a central location (i.e., the HHU in Düsseldorf), and will have a duration of approximately 3.5 h starting at a time which is feasible and familiar to GPs (late afternoon/early evening on Wednesdays and Fridays, or on Saturdays). In order to avoid seasons of high workload, and to avoid a low reach of patients during holiday periods, study cycles will primarily be carried out during the months February/March 2018/2019, September/October 2017/2018, and May/June 2018/2019 **(**Fig. 1**)**.

Both types of training will include an introductory lecture of approximately 60 min about tobacco addiction, evidence-based smoking cessation treatments, and about the specific method of stop-smoking advice (either 5A or ABC). Reflexive units and discussions on GPs’ experience with the provision of stop-smoking advice, and on associated barriers and facilitators, will also be a part of the introductory lecture.

This lecture will be followed by an intensive role play of about 90–120 min with professional actors trained in patients’ specific behaviour. In these role plays, GPs get to practise the respective training method and receive moderated feedback (see below for further details regarding the content). Training sessions will always be led by a pair of trainers: a senior researcher of the study centre and an experienced GP (peer-trainer) who can specifically address the questions and needs of daily GP routine. For both types of training, the number of participants will be restricted to a minimum of three and a maximum of ten (in case of participating group practices). A detailed manual has been developed which the trainers should refer to. Thus, we aim to standardise the contents, schedule, and quality of each training session as much as possible. In order to avoid that the quality of training sessions differs between 5A and ABC, and might thus impact the study outcome, we will rotate the pairs of trainers from study cycle to study cycle. Face validity of the training was assessed during the pilot study and will be assessed again during a test run prior to the start of the main trial, where trainers, actors, and two practicing GPs will rehearse and review the clinical vignettes for the role plays which have been planned in close collaboration with the CoMeD at the HHU Düsseldorf.

The CoMeD team is engaged in the training of professional actors to become an SP and learn how to give constructive feedback for simulated role plays in medical communication education. Different types of, for example tobacco addicted, patients can be portrayed by one SP. These SP trainings are a major element in order to guarantee high quality education of patient-physician-communication [40].

Both trainings will teach GPs how to ask patients about smoking (A1) and how to advise them to stop (A2). The 5A training will specifically teach GPs how to: assess the patients’ willingness to quit (A3) and how to apply the 5R approach in patients who are not willing to quit; assist the quit attempt (A4); and arrange follow-up (A5). The ABC training will specifically teach GPs how to make the offer of treatment (A4) opportunistically (e.g., a prescription for NRT, or a referral to individual or group behavioural support; irrespective of the patients’ motivation to stop at the time of the consultation). In addition to the training, GPs from both intervention groups will receive paper-based leaflets summarising the key aspects of 5A or ABC, a one-page handout with short information on evidence-based smoking cessation treatments which can be offered to patients, as well as a one-page copy template with several local outpatient programs to which smoking patients can be referred to. The completion of the training, irrespectively of the method, will be incentivised with Continuing Medical Education (CME) credits. Material for GPs of both groups will be of exactly the same quality and adhere with common standards for CME.

Considering the above, it can be assumed that the 5A training would require more time than the ABC training. However, during the pilot study, we noticed that teaching the ABC method demands extra time for group discussions on offering smoking cessation treatment irrespective of patients’ motivation to stop, as GPs seem less familiar with this opportunistic approach. Hence, duration was kept the same for both trainings.

### Theoretical foundation of the intervention: COM-B model

The theoretical foundation of the intervention is based on the “COM-B” model developed by Michie and colleagues [27]. According to this model, the interaction between the three components capability (C), opportunity (O), and motivation (M) causes the performance of behaviour (B). Each component influences behaviour and, moreover, capability and opportunity influence motivation and therefore affect behaviour. COM-B is a dynamic model whereby performance of a specific behaviour can in turn influence capability, opportunity, and motivation. Interventions need to change one or more of the components in such a way as to put the system into a new configuration. Interventions need to change one or more of the components in such a way as to achieve a desired change in behaviour.

According to studies which explored barriers to the promotion of smoking cessation in German primary care, GPs often lack the feeling of competence in giving cessation advice (capability: knowledge, practical skills) [17–19], inadequate reimbursement of costs (opportunity) involved in the promotion of smoking cessation and, additionally, rate these conversations to be too time consuming (capability, motivation) [17, 41]. In our trainings, we aim to address at least these two components (capability and motivation) of the COM-B Model and expect that this might affect the GPs’ behaviour of offering brief stop-smoking advice to their smoking patients during routine consultation. Moreover, it can be hypothesised that giving brief stop-smoking advice according to ABC might influence the component opportunity because this method is less difficult and less time consuming to apply, and can be integrated more easily into the daily practice routine.

For a better description of the main active elements of the developed trainings, we aim to use the Behaviour Change Techniques (BCT) Taxonomy from Michie and colleagues [42]. A training session can be categorised in three superordinate elements: (1) introductory lecture, (2) practice element with role plays, and (3) reflexive elements. Reflexive elements, however, also occur in group discussions during the role plays or following the introductory lecture. BCTs that will be applied during each training session are listed in Table 1.

**Table 1 Tab1:** Exemplary contents of the ABC and 5A training with corresponding codes and labels according to the Behavior Change Technique (BCT) Taxonomy^a^

Superordinate elements of training	BCT group^a^	BCT code and label^a^	Examples from the training or training manual
1 Introductory lecture	1 Goals and planning	1.2 Problem solving	Prompt GPs to identify barriers preventing them from starting a conversation on smoking cessation during routine consultations and discuss potential solutions. For example how to advise patients with multiple unsuccessful quit attempts in their history, how to start a conversation on smoking cessation with patients having no smoking-related problems.
	4 Shaping knowledge	4.1 Instruction how to perform the behaviour	Inform GPs verbally on how to provide brief advice to stop-smoking according to 5A/ABC with examples of different types of patients.
	5 Natural consequences	5.1 Information about health consequences	Inform GPs verbally on health risks of smoking and benefits of smoking cessation, and on the role of GPs in reducing smoking prevalence on a population level.
		5.6 Information about emotional consequences	Pointing out that the provision of brief-stop smoking advice aims at triggering a quit attempt rather than long-term abstinence in every smoker receiving such an advice. Lowering high or delusive expectation should lead to a reduction of frustration, and thus increase self-efficacy. Only ABC training: Provide information on how application of the ABC method to deliver brief-stop smoking advice (without discussing patients’ motivation to quit) can reduce stress and frustration in daily GP routine, and thus increase satisfaction.
	6 Comparison of behaviour	6.1 Demonstration of the behaviour	Demonstrate to GPs how to raise the issue of smoking cessation with patients indirectly via pictures of exemplary patient-physician conversations.
		6.2 Social comparison	Providing information on the proportion of smokers in Germany who were offered GP advice on quitting by their GP, thus they can compare with their own performance.
		6.3 Information about others’ approval	Telling GPs that smoking patients will appreciate a conversation on smoking cessation including the provision of support/assistance rather than a conversation with criticism or reproaches causing feelings of guilt in patients.
	7 Associations	7.1 Prompts and cues	Provision of handouts for GP practice rooms to remind them of delivering brief stop-smoking advice to all smoking patients: including: the 5A/ABC method, behaviour change techniques for patients (e.g. setting a quit day), the Fagerström Test for Cigarette Dependence^b^, information on evidence-based smoking-cessation therapy, contact information: smokers’ telephone helpline, regional group-based smoking cessation programs).
	8 Repetition and substitution	8.2 Behaviour substitution	ABC: Suggest that GPs should not ask for patients’ motivation to stop smoking and provide their assistance instead to every smoking patient regardless of motivational status. 5A/ABC: Suggest that GPs provide stop smoking support as a brief or very brief conversation on smoking cessation rather than as a time consuming and exhausting discussion.
	9 Comparison of outcomes	9.1 Credible source	Presentation of evidence-based data (e.g., data from Cochrane reviews) on the importance and effectiveness of brief GP advice to stop-smoking.
	11 Regulation	11.2 Reduce negative emotions	Advise GPs how to reduce frustration during stop smoking conversations (e.g., through realistic goal setting: aiming to trigger a quit attempt rather than long-term abstinence in smoking patients).
	13 Identity	13.2 Framing/reframing	Cognitive structuring: Suggest that medical advice on quit smoking must not necessarily be time consuming and exhausting (which are frequently reported barriers preventing GPs from raising a stop-smoking conversation).
2 Practice elements (Role plays with peer feedback)	1 Goals and planning	1.1 Goal setting (behaviour)	GPs are encouraged to apply all the steps of ABC/5A during the role play and therefore change their familiar patterns of behaviour during conversations on smoking cessation.
		1.2 Problem solving	Discussions during role plays: prompt GPs to identify barriers preventing them from applying a specific step of 5A or ABC (“Which steps of 5A or ABC could you (not) apply during the role play, and why or why not?” “What could have helped/could be changed during in this situation?”).
		1.5 Review behaviour goal(s)	Examine how well a GP’s performance during role play corresponds to agreed goals (e.g., applying all steps of the 5A/ABC method, or providing brief advice on quitting to the patient without reproaches or criticism); and consider a modification of a behavioural goal, e.g. through realistic goal setting: aiming to trigger a quit attempt rather than being responsible for the quit attempt’s success.
		1.6 Discrepancy between current behaviour and goal	Trigger a quit attempt rather than long-term abstinence in smoking patients; Trainer and peers point out and discuss which steps of 5A or ABC had not been applied during role play.
	2 Feedback and monitoring	2.2 Feedback on behaviour 2.7 Feedback on outcomes of behaviour	Peers and trainers provide moderated feedback on GP’s behaviour/ performance and on observed outcomes (reactions) of patient (actor) during role plays.
	3 Social support	3.2 practical support 3.3 emotional support	Peers and trainers provide practical and emotional support during role plays: e.g., advise on how to cope with a specific patient reaction.
	4 Shaping knowledge	4.1 Instruction how to perform the behaviour	Repeated instructions (verbal) are provided by the trainers prior to the role plays: how to provide brief advice to stop-smoking according to 5A/ABC.
	5 Natural consequences	5.4 Monitoring of emotional consequences	GPs are encouraged to reflect and reveal their feelings during active role play.
	6 Comparison of behaviour	6.1 Demonstration of the behaviour	Provision of role plays with moderated feedback to practice the delivery of brief stop-smoking advice according to 5A/ABC.
		6.2 Social comparison	GPs are encouraged to observe the performance of colleagues during role play allowing comparisons with their own performance during role play but also during past routine practice consultation.
		6.3 Information about others’ approval	Peers and trainers provide feedback on the performance of the GP who participates in the role play.
	8 Repetition and substitution	8.1 Behavioural practice/rehearsal	Provision of role plays with moderated feedback to practice the delivery of brief stop-smoking advice according to 5A/ABC.
		8.2 Behaviour substitution	Trainer and peers suggest alternative reactions/sentences during role plays corresponding to the 5A/ABC method (e.g., ABC: providing assistance with attempt to quit rather than discussing patients’ motivation to quit smoking).
	9 Comparison of outcomes	9.1 Credible source	GP peer trainer reports on own positive experiences but also on challenges with the provision of brief stop-smoking advice according to either the 5A or ABC method.
	13 Identity	13.2 Framing/reframing	Providing measurements on the exact duration (minutes) of role-play in order to demonstrate that the provision of brief advice on quit smoking must not necessarily be time consuming, which is a frequently reported barrier preventing GPs from raising a stop-smoking conversation.
3 Reflexive elements (Group discussions at the beginning and end of the training)	1 Goals and planning	1.1 Goal setting (behaviour)	Prompt GPs to set a self-defined goal for the next working day regarding the provision of brief stop-smoking advice with the so-called “Monday-Question”: “What would you change/ do differently next Monday in practice?”.
	9 Comparison of outcomes	9.2 Pros and cons	Encouraging GPs to reflect the advantages and disadvantages of providing brief stop-smoking advice (more often) to their smoking patients.
	13 Identity	13.3 Incompatible beliefs	Drawing attention to discrepancies between GPs’ current or past performance regarding the provision of advice to quit smoking and his or her self-image as a health consultant.
	15 Self-belief	15.3 Focus on past success	Encourage GPs to reflect strategies which helped them in the past to have a successful conversation on smoking cessation with a patient.

^a^Taken from Michie, S., Richardson, M., Johnston, M., Abraham, C., Francis, J., Hardeman, W., Eccles, M. P., Cane, J. & Wood, C. E. (2013). The Behavior Change Technique Taxonomy (v1) of 93 Hierarchically Clustered Techniques: Building an International Consensus for the Reporting of Behavior Change Interventions. Annals of Behavioral Medicine, 46(1), pp. 81–95. doi: 10.1007/s12160-013-9486-6. Available from: https://link.springer.com/article/10.1007/s12160-013-9486-6. (Accessed 30.07.2018)

^b^Fagerström, K. Determinants of Tobacco Use and Renaming the FTND to the Fagerström Test for Cigarette Dependence Nicotine Tob Res (2012) 14 (1): 75–78

### Outcomes

#### Primary outcome

The primary outcome is defined as the number of patients who report the receipt of brief stop-smoking advice during the last consultation with their GP, irrespective of the training method, out of the total number of patients who stated to be current tobacco smokers at the time of the consultation with their GP. These data will be collected prior to and following the training through personal interviews in all consecutive patients immediately following GP consultation.

#### Secondary outcomes

Secondary outcomes S1–3 will be collected together with the primary outcome through personal interviews immediately after GP consultation and refer to the patients’ last consultation with their GP. Data on secondary outcomes S4–9 will be collected by means of three follow-up questionnaires by postal dispatch. The denominator of all secondary outcomes is the number of patients who stated to be current tobacco smokers at the time of the consultation with their GP.S1: Number of patients who report the receipt of a recommendation for individual or group behavioural support for smoking cessation;S2: Number of patients who report the receipt of a recommendation or prescription of NRT for smoking cessation;S3: Number of patients who report the receipt of a recommendation or prescription for varenicline or bupropion for smoking cessation;S4–6: patient-reported rates of quit attempts after 4, 12, and 26 weeks following the consultation with the GP;S7–9: patient-reported point prevalence abstinence rates at 4, 12, and 26 weeks following the consultation with the GP;S10: Interaction effect between time (from pre-to post-training) and group variable (5A vs. ABC) for the primary and secondary outcomes S1-S9.

Furthermore, this study aims to assess additional data in GPs on to what extent one 3.5-h-training session according to either the 5A or the ABC method affects, at least in the very short-term (immediately following the training), self-perception of GPs’ attitude towards (motivation), knowledge on, and practical skills (capability) in the provision of brief advice to quit tobacco consumption.

### Data collection

#### General practitioners

A brief questionnaire will be administered to GPs prior to the training to collect information on the characteristics of the participating GPs (including age, gender, smoking status, professional experience, and specialisation) and the practice characteristic, such as location (rural vs. urban), average number of patients per calendar quarter.

Within the 4 weeks prior to and immediately following the training, GPs will be asked to fill out a brief questionnaire to collect data on their attitude towards (motivation), knowledge on, and practical skills (capability) to provide brief stop-smoking advice during routine consultations. In this questionnaire, GPs will be asked to indicate whether they are aware of the steps of the designated method, whether they provide brief stop-smoking advice regularly or not, whether they think that providing brief advice to their smoking patients is important, effective, and feasible in GP practices, and whether they are confident in providing such advice, respectively according to either 5A or ABC. Answering options will be: (1) “strongly support”, (2) “support”, (3) “tend to support”, (4) “oppose”, (5) “strongly oppose”.

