### Study design

The finalised training will be evaluated in a pragmatic 2-arm cRCT with a pre-post-design (pre-training = care as usual) for the primary outcome, and a cluster randomisation for secondary outcome (comparison of the effectiveness of both training methods - 5A and ABC – against each other) in approximately 48 GP practices (cluster) in NRW (Germany) between June 2017 and February 2020. The intervention will be a 3.5-h-training for GPs in providing brief stop-smoking advice according to the 5A or ABC method. Data on primary and on several secondary outcomes will be collected prior to and following the training by interviewing consecutive patients of participating GPs. Further secondary data will be collected by means of three follow-up questionnaires.

In total, there will be six study cycles with 8 participating GP practices per cycle. A study cycle is defined as a period of 8 weeks with the training of GPs from four practices in the 5A method and GPs from four practices in the ABC method in the middle of this period. Data collection will be carried out on approximately seven varying GP office days during the 4-week pre-training period and on 7 days during the 4-week post-training period. Thus, we aim to minimise sampling bias which could result from considerable fluctuations in patient flow among different days or weeks of data collection (e.g., on Mondays, during flu epidemic, or on holidays). The distribution of study cycles over the total duration of the study is shown in the Gantt chart of the study (Fig. 1).

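### The pre-training GP questionnaire may be completed at any time in the weeks that supply the care-as-usual advice rate and, as described, asks about the allocated method, so it could cue the behaviour being measured

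*Protocol article*

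**What the plan says.** **Timing of the form.** Protocol article, Data collection, General practitioners: "Within the 4 weeks prior to and immediately following the training, GPs will be asked to fill out a brief questionnaire". No day within the 4 weeks is fixed.

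**Content of the form.** The same paragraph says "GPs will be asked to indicate whether they are aware of the steps of the designated method". Further items are "whether they provide brief stop-smoking advice regularly or not", whether advice is important, effective and feasible, and "whether they are confident in providing such advice, respectively according to either 5A or ABC". The form itself is not reproduced. The additional files that the article cites are the patient interview and follow-up forms.

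**The comparator.** The Study design section treats the pre-training period as care as usual and collects its patient data on "approximately seven varying GP office days during the 4-week pre-training period".

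**Masking.** The Blinding section says "we aim to reduce the information on the group allocation until the end of the 4-week pre-training data collection period". Until then GPs are to know only that brief advice is being examined and that two methods are compared, and it adds: "The GPs, however, received no information about the content and the difference of both methods". The reason given is possible bias "where GPs tend to make more effort in delivering brief advices to quit depending on the training method they were allocated to".

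**The concern.** The questionnaire and the pre-training patient interviews share one 4-week window. A GP who completes the form early in it still has collection days ahead, after being asked about a named method and about his or her own advice-giving.

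The protocol treats this kind of prompt as a threat elsewhere. It conceals the smoking topic from patients before the consultation so that they do not raise it themselves. Table 1 lists reflection on one's own advice-giving as an active technique of the training. A form that asks GPs to appraise their own practice is a weak version of the same thing.

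Two results are at stake:
- **Primary outcome.** A raised pre-training rate shrinks the pre-post difference.
- **S10.** If naming one method prompts more than naming the other, the arms differ before training and the time-by-group interaction is distorted.

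**Working it through.** **Step 1: can the form fall inside the collection window?** The form is due within the 4 weeks before training. Patient data come from about 7 days spread over the same 4 weeks. No section sets an order between the two, so the overlap is permitted but not required.

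**Step 2: does the form carry what the Blinding section holds back?** The words designated and respectively most naturally mean that each GP is asked about the allocated method. That would disclose the allocation. It need not teach the steps, because asking whether someone knows them is not the same as listing them.

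**Step 3: reproduce the plan's figures.** Inputs from Power and sample size: 18% before training; 23% (5A) and 33% (ABC) after; 48 practices; logit SDs 0.40 (practices) and 0.05 (time effect).
- Odds ratio for 18% to 28%: (0.28/0.72) / (0.18/0.82) = 1.772, against the stated 1.77.
- Simulated power with 8 + 8 patients per practice: about 86%, consistent with the stated minimum of 80%. The simulation fitted a logistic mixed model with random practice and time effects and no covariates, using a Wald test at 1.96. It used 300 runs at 8 + 8 and 150 at 21 + 21.

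**Step 4: illustrate a raised pre-training rate.** The rise is an assumption; post-training rates are left unchanged. By hand, average the two arms on the logit scale:
- Post-training odds: 0.23/0.77 = 0.2987 and 0.33/0.67 = 0.4925; geometric mean = √(0.2987 × 0.4925) = 0.3836.
- Pre-training odds: 0.2195 (18%), 0.2500 (20%), 0.2821 (22%).
- Odds ratio = 0.3836 / pre-training odds.

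| Pre-training rate | OR by hand | OR simulated (8 + 8) | Power, 8 + 8 | Power, 21 + 21 |
|---|---|---|---|---|
| 18% (plan) | 1.75 | 1.77 | 86% | not run |
| 20% (assumed) | 1.53 | 1.54 | 69% | 96% |
| 22% (assumed) | 1.36 | 1.36 | 40% | 79% |

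**Step 5: dilution.** If the form is completed with a fraction f of the collection still to come and raises the rate on those days by c points, the window average rises by f × c. At the midpoint (f = 0.5), a 2-point rise in the average needs c = 4, and a 4-point rise needs c = 8.

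**Step 6: direction for S10.** With equal pre-training rates the planned ratio of odds ratios (ABC over 5A) is 0.4925/0.2987 = 1.65.
- If only the ABC pre-training rate rose to 20%: 1.65 × 0.2195/0.2500 = 1.45.
- If only the 5A pre-training rate rose to 20%: 1.65 × 0.2500/0.2195 = 1.88.

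The bias can go either way.

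**The case against.** A reader might infer that the data-collection and blinding sections contradict each other outright. They do not. No day is fixed, so a form completed after the last collection day satisfies both, and the Blinding section states an aim while conceding that GPs cannot be fully blinded.

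A reader might also take disclosure of the allocation as established. The form is not shown, and one summary sentence describes both the before and the after versions.

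The extra cue may be small. GPs already know that brief advice is being studied, have agreed to be trained in it, and have a researcher recruiting in the waiting room. Nothing in the documents shows that the form raises advice-giving. For the primary outcome the bias would run towards the null, so it could not create a false claim of benefit. The planned 21 + 21 patients per practice also exceed the 8 + 8 that the primary analysis needs.

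All of this stands, and it limits the point without removing it. No section keeps the form out of the collection window. The argument in Strengths and limitations that reactivity does not distort a pre-post difference concerns the researcher's presence, which is common to both periods. It does not cover a prompt introduced partway through the first period.

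**Conclusion.** The point holds as a risk that the plan leaves open. The questionnaire's timing is too loose and its described wording too specific to sit safely beside the Blinding section's aim. It is worth correcting because the pre-training rate is the only comparator for the primary outcome.

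Its size is unknown. The odds ratios of 1.54 and 1.36 show sensitivity to assumed pre-training rates of 20% and 22% averaged over the whole window, with no carry-over into the post-training rate. They are not estimates, and it would be wrong to read from them that a given share of the effect will be lost. With 21 + 21 patients per practice, simulated power stays at 96% and 79% in these two cases. The S10 bias additionally requires a cue that differs by method, and the documents indicate neither whether it would nor in which direction.

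**What to change.** State in Data collection, General practitioners that the before questionnaire is completed after the last pre-training collection day in that practice and before training begins. The training venue, immediately before the introductory lecture, is the simplest place. Use one form, identical in both arms, that does not identify the allocated method. It should not list the steps of either method, since that would give away the item on awareness of the steps. Align the Blinding section with this.

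The cost is a small change of timing and wording, plus a few minutes at a session the GPs attend anyway. For cycles already completed, report each form's completion date relative to that practice's collection days, so that readers can see how much of the pre-training data could have been affected.
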